### 5.4.12 6-Month Follow-up (±30 days)

At 6 months post-procedure, subjects must return for follow-up including:

- Physical exam (height, weight, waist & hip circumference, office BP).
- Antidiabetic medication/insulin use.
- Other treatments (cardiovascular, anticoagulant, antiplatelet therapies).
- Laboratory tests: CBC, renal function (BUN, creatinine, eGFR), fasting glucose & insulin, 14-day CGM, HbA1c, HOMA-IR & HOMA-β, lipid profile, liver function (ALT, AST, ALP, TBil, GGT), plasma catecholamines.
- HRV: 24-hour Holter monitoring.
- AE assessment and management (AE, SAE, SADE, UADE, USADE, ADE).
- OGTT (5-point)
- 14-day CGM.
- Insulin and C-peptide secretion tests (5-point), HOMA-IR, HOMA-β.
- CTA and/or DSA to assess vascular patency.
- EQ-5D-5L quality of life questionnaire.

Note: Subjects with CTA showing >50% stenosis at EDN sites must undergo DSA. If CTA is normal, DSA is not required. Metformin must be withheld on the day of CTA or DSA.

### 5.4.13 12-Month Follow-up (±30 days)

At 12 months post-procedure, subjects must return for follow-up including:

- Physical exam (height, weight, waist & hip circumference, office BP).
- Antidiabetic medication/insulin use.
- Other treatments (cardiovascular, anticoagulant, antiplatelet therapies).
- Laboratory tests: CBC, renal function (BUN, creatinine, eGFR), fasting glucose & insulin, 14-day CGM, HbA1c, HOMA-IR & HOMA-β, lipid profile, liver function (ALT, AST, ALP, TBil, GGT), plasma catecholamines.
- AE assessment and management (AE, SAE, SADE, UADE, USADE, ADE).

.

### 5.4.14 24-Month Follow-up (±30 days)

At 24 months post-procedure, subjects must return for follow-up including:

- Physical exam (height, weight, waist & hip circumference, office BP).
- Antidiabetic medication/insulin use.
- Other treatments (cardiovascular, anticoagulant, antiplatelet therapies).
- Laboratory tests: CBC, renal function (BUN, creatinine, eGFR), fasting glucose & insulin, 14-day CGM, HbA1c, HOMA-IR & HOMA-β, lipid profile, liver function (ALT, AST, ALP, TBil, GGT), plasma catecholamines.
- AE assessment and management (AE, SAE, SADE, UADE, USADE, ADE).

### 5.4.15 End of Study

The study will conclude after all enrolled subjects have completed 24 months of follow-up, or have withdrawn (due to death or loss to follow-up), or exceeded the final visit window (>30 days). Data collected will be used to evaluate all study endpoints. Any subsequent adverse events will be managed according to standard clinical care by the treating physician.

###

### 5.4.16 Source Documents

Copies of preserved original paper records and printouts of original electronic records shall be declared as true copies of the source documents and must be signed and dated by a member of the study site team.

## 5.5 Device Use Specifications

### 5.5.1 Surgical Technique

This study uses the endovascular denervation (EDN) system (generator and catheter) manufactured by Shanghai Brattea Medical Technology Co., Ltd. to perform EDN in the celiac trunk, common hepatic artery, and/or proper hepatic artery for the treatment of T2DM. The operating physician and associated staff must receive adequate training on use of the investigational devices prior to the procedure and follow the surgical workflow below.

### 5.5.2 Surgical Workflow

#### 5.5.2.1 Pre-procedure Preparation

① Prepare the EDN generator, EDN catheter, and procedural consumables in advance. Place the generator in a position convenient for observation and operation, with the display facing the operator.

② Position the subject supine on the operating table. Firmly attach the neutral (return) electrode to the buttock. Perform routine disinfection and draping of the right groin.

#### 5.5.2.2 Pre**-**EDN Angiography

① Identify a puncture site ~1 cm inferior to the midpoint of the right groin; infiltrate with 2% lidocaine for local anesthesia.

② Perform right femoral arterial access using the Seldinger technique and place an 8F vascular sheath.

③ Advance a 5F pigtail catheter over a 0.035-inch hydrophilic (loach-type) guidewire through the sheath; position the catheter tip at the superior margin of T12 and perform abdominal aortography (DSA) to delineate the morphology and course of the celiac axis and branches, and to confirm whether angiographic exclusion criteria are present.

④ If no angiographic exclusion criteria are met, the subject may be enrolled in this clinical study.

⑤ Remove the pigtail catheter. Using a coaxial technique, advance a 5F hepatic artery catheter (Rh catheter) and an 8F guiding catheter over a 0.035-inch guidewire. Position the tip of the guiding catheter in the proper hepatic artery.

#### 5.5.2.3 EDN Procedure

Target vessels for ablation in this study are the celiac trunk, common hepatic artery, and/or proper hepatic artery. Steps:

① Determine target vessel anatomy and diameter by angiography to select an appropriately sized ablation catheter.

② After removing the Rh catheter, advance the 6-electrode EDN ablation catheter (manufactured by Shanghai Brattea Medical Technology Co., Ltd.) through the guiding catheter into the target vessel (see the product IFU for catheter operation).

③ Connect the RF system per the generator IFU and perform generator self-check.

④ Expand the distal basket and appose the electrodes to the vessel wall using the handle controls. Assess wall contact via displayed temperature and impedance (temperature ~37 °C, impedance <400 Ω) and adjust as needed.

⑤ Once adequate wall contact is confirmed, set RF parameters (temperature 60 °C; ablation time 120 s).

⑥ Begin RF ablation under IV analgesia/sedation (see Section 5.4.7.6). Continuously monitor real-time power, impedance, and temperature.

⑦ After each ablation, perform DSA to evaluate vessel morphology and detect complications. If vasospasm is observed, pause manipulation and reimage after 5 minutes. If spasm persists, slowly administer papaverine or nitroglycerin via the guiding catheter and reassess after 5 minutes.

⑧ Repeat RF ablation in the celiac trunk, common hepatic artery, and/or proper hepatic artery as required. Maintain adequate anticoagulation, sedation, and analgesia intraoperatively.

⑨ After completing ablation in all three segments, remove the ablation and guiding catheters; reintroduce the pigtail catheter and perform celiac angiography.

⑩ Upon confirming no significant abnormalities at ablation sites, remove all catheters. Close the arterial puncture using a Cordis vascular closure device/ProGlide suture-mediated device and apply local compression dressing. When dorsalis pedis or posterior tibial pulses are normal, the procedure is complete and the subject is transferred back to the ward.

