**Figure 3-5 Self-Check Interface**

This interface requires that the SD card be properly installed. Upon power-on, the device automatically performs a self-check of internal modules, including the power supply module, temperature board, LCD screen, and RF board. A check mark indicates that the module has passed the self-check. A cross mark indicates failure. This provides an indication of whether the device can function normally. If a module fails, a fault message will appear (detailed descriptions of error codes can be found in the user manual).

1. Settings Interface (Figure 3-6)

The settings interface allows adjustment of temperature, RF duration, maximum impedance, minimum impedance, and parameter storage. The left and right triangular buttons decrease or increase values, respectively. The save icon button stores the adjusted parameters, which are simultaneously displayed in a reference table. Saved parameters can be recalled by directly selecting the corresponding entry.

[figure not shown]

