**Figure 3-9 Curve Display Interface**

This interface primarily shows time-dependent curves of temperature, power, and impedance. A “Back” button at the top allows return to the data recording interface. The interface can also be switched directly to the settings interface or the operation interface.

(3) RF Generator Procedural Steps

1) Pre-procedural

① Position the generator and catheter connection cable near the operating table for convenient observation and operation.

② Connect the grounding terminal on the rear panel of the generator to earth using the grounding cable.

③ Connect the prepared catheter and surface electrode pad to the generator.

④ Insert the power cable into the generator’s power socket and connect the other end to the mains outlet.

1. Intra-procedural

① Switch on the generator. The LCD screen will light up and the system will initiate a self-check. After approximately 20 seconds, the device enters standby mode once the self-check is complete.

② Place the prepared surface electrode pad on the patient’s buttock with the conductive side facing upward.

③ Introduce the ablation catheter, confirm correct placement, and ensure that the RF electrodes are in proper contact with the target tissue.

④ Set the required temperature, impedance, and RF duration using the control buttons. The selected values will appear in the corresponding display windows, and successful input will be indicated on the LCD screen.

⑤ Press the diagnostic icon to initiate wall-contact testing. Observe the target temperature: a gradual rise indicates good wall contact, whereas no increase or abrupt fluctuations indicate poor contact. Catheter adjustments may be performed and the test repeated. Any electrode can be selectively disabled by toggling its icon.

⑥ Press and hold the RF button or the foot switch for 3 seconds to start RF ablation. The generator will emit an audible signal and the countdown timer will begin. RF ablation ends automatically when the countdown reaches zero. During ablation, continuously monitor the real-time values of power, impedance, and temperature. If necessary, ablation parameters may be readjusted. To terminate RF prematurely, press the RF button or foot switch again; RF output and the audible signal will stop. To resume RF delivery, restart the activation sequence.

1. Post-procedure

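### The surgical workflow runs the generator self-check after the EDN catheter is in the target artery; it should come before the catheter enters the patient, preferably before arterial puncture

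*Protocol*

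**What the plan says.** Section 5.5.1 requires the operating physician and staff to follow the workflow set out in Section 5.5.2. Within it:

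- **5.5.2.1** has the generator prepared in advance and placed with its display facing the operator. It does not ask for the generator to be switched on or checked.
- **5.5.2.2** covers femoral access, aortography and positioning of the guiding catheter in the proper hepatic artery.
- **5.5.2.3 step ②** advances the EDN catheter "through the guiding catheter into the target vessel".
- **5.5.2.3 step ③** reads "Connect the RF system per the generator IFU and perform generator self-check".
- **5.5.2.3 step ④** reads "Expand the distal basket and appose the electrodes to the vessel wall using the handle controls".

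Section 3.3.2.2, under RF Generator Procedural Steps, orders these actions differently. Intra-procedural step ① is "Switch on the generator. The LCD screen will light up and the system will initiate a self-check", followed by "After approximately 20 seconds, the device enters standby mode once the self-check is complete". Step ③ is "Introduce the ablation catheter, confirm correct placement".

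The description of the self-check interface in the same section says: "Upon power-on, the device automatically performs a self-check of internal modules". It names the power supply, temperature board, LCD screen and RF board, and adds: "This provides an indication of whether the device can function normally".

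**The concern.** A readiness check is most useful before the step that depends on it. Here the workflow that operators are told to follow places the check after the investigational catheter has reached the target artery, and the protocol's own generator instructions place it before.

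Enrolment makes the order matter slightly more. Sections 5.2.3.1, 5.4.3 and 5.4.8 all tie it to insertion of the EDN catheter (into the body or into the guiding sheath, depending on the section). A generator that failed at step ③ would therefore be discovered in a subject who was already enrolled and already exposed to the investigational catheter, with no treatment yet possible. That exposure would have served no purpose.

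**Working it through.** No formula applies; the check is a comparison of printed sequences.

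| Action | Surgical workflow (5.5.2) | Generator steps (3.3.2.2) | Catheter instructions (3.3.2.2) |
|---|---|---|---|
| Catheter connected to generator | 5.5.2.3 ③ | Pre-procedural ③ | ⑤ |
| Generator self-check | 5.5.2.3 ③ | Intra-procedural ① | Not mentioned |
| EDN catheter enters the patient | 5.5.2.3 ② | Intra-procedural ③ | ④ (guiding sheath), ⑥ (target artery) |
| Basket expanded | 5.5.2.3 ④ | Not a separate step | ⑦ |
| RF delivered | 5.5.2.3 ⑥ | Intra-procedural ⑥ | ⑧ |

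1. **Order.** In the surgical workflow the catheter is in the target vessel at ② and the self-check follows at ③. In the generator steps the self-check is at ① and catheter introduction at ③. The two actions are reversed.
2. **Does the check need the catheter in place?** No. It starts by itself at power-on, and every module named is inside the generator. Whether the generator recognises the catheter is a separate matter, and Table 5-3 records it as a separate item from the self-check at startup.
3. **Which list governs?** Section 5.5.1 points operators to Section 5.5.2; the generator steps sit in the device description. The less favourable order is therefore the operative one.
4. **Is the gap closed elsewhere in the workflow?** Section 5.5.2.1 calls for advance preparation but not for switch-on or a passed check. An earlier check is allowed but not required.
5. **What exposure is added?** By the end of 5.5.2.2 the guiding catheter is already in the proper hepatic artery, and the basket is not expanded until 5.5.2.3 ④. A fault found at ③ therefore adds only the placing and withdrawing of an unexpanded EDN catheter.
6. **How often?** The protocol gives no self-check failure rate, so no probability can be stated.

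**The case against.** The case for leaving this alone has several parts.

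- **The instructions for use may settle it.** Step ③ refers to the generator IFU, which is not at hand. If the IFU mirrors the generator steps in Section 3.3.2.2, staff trained on the device would already check first. This limits the finding to the printed order. The reference is attached to connecting the system, however, and does not undo a sequence that puts the self-check after catheter advancement.
- **The generator steps are a general description.** They also place the return pad on the patient after switch-on, whereas 5.5.2.1 attaches it during preparation, and the catheter instructions give a third order for connection. It is true that the three lists disagree on when to connect. The catheter instructions say nothing about the self-check, so they do not support doing it late.
- **The check still precedes any energy delivery.** Correct, and this is the main reason the point is minor. The printed order protects against ablating with a faulty generator; it does not protect against placing a catheter needlessly.
- **Moving the check only to just before step ② gains little.** This stands. By then the subject has had femoral puncture with an 8F sheath, aortography and guiding-catheter placement. A check before puncture avoids all of that if the generator is faulty.

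**Conclusion.** The point holds, at low severity. The printed workflow in 5.5.2.3 reverses the order in the protocol's own generator steps, and nothing in the document gives a reason for the later check. The order itself is certain from the text. The practical consequence, a fault found only after catheter exposure and enrolment, assumes that operators follow Section 5.5.2 as printed and do not check earlier of their own accord.

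It is a small operational safety improvement. The ITT definition in Section 6.4 already covers enrolled subjects in whom EDN was not completed, and no objection is made to it.

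**What to change.** - **Section 5.5.2.1:** add that the generator is switched on and has passed its self-check before arterial puncture. If that is impracticable, the latest acceptable point is before step ② of 5.5.2.3, which still avoids needless EDN catheter exposure but not the access procedure.
- **Section 5.5.2.3 step ③:** remove the self-check. Keep the connection of the RF system, and have the operator confirm that the generator recognises the catheter and detects the surface electrode. Both are already items in Table 5-3.
- **Leave unchanged:** the generator steps in 3.3.2.2, the enrolment definition and the ITT set. Continue to record self-check failures in Table 5-3 and as device deficiencies under Section 12.5.

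The cost is a wording change in Section 5.5.2. The check takes about 20 seconds wherever it is placed, and no procedure or data item is added.

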# 6. Statistical Considerations

## 6.1 Primary Endpoints

Primary Safety Endpoint

Incidence of composite major adverse events (MAE)* related to the investigational device and/or ablation procedure occurring intraoperatively or within 30 days after the baseline procedure.

* MAE includes:

- Hypoglycemia or hyperglycemia requiring hospitalization.
- Vascular complications requiring surgical repair, interventional therapy, thrombin injection, or blood transfusion.
- Celiac/hepatic artery dissection or perforation requiring intervention.
- Significant embolic events causing end-organ damage or requiring intervention to prevent end-organ damage.
- Acute liver injury or liver failure.
- All-cause mortality.

**Primary Efficacy Endpoint**

Change in HbA1c at 6 months post-procedure compared with baseline.

## 6.2 Study Hypothesis

This is a single-arm feasibility clinical trial designed to explore the safety and efficacy of the EDN generator and catheter manufactured by Shanghai Brattea Medical Technology Co., Ltd. for the treatment of T2DM; therefore, no formal statistical hypothesis is specified.

## 6.3 Sample Size

A total of 30 subjects will be enrolled to support the study objectives.

## 6.4 Statistical Methods

**Statistical Analysis Sets**

Primary, secondary, and additional endpoints will be analyzed using both the Intent-to-Treat (ITT) and Per-Protocol (PPS) populations.

ITT: All subjects who signed written ICF and were enrolled, regardless of whether EDN was successfully performed.

PPS: Subjects who underwent EDN in the celiac/hepatic arteries using the investigational device.

**Control of Bias/Systematic Error**

Data from all study centers will be pooled for analysis.

**Enrollment by Center**

Given the small sample size of this feasibility trial, no upper limit is set per site; competitive enrollment will be used.

**Data Analysis**

As a single-arm feasibility study, no formal hypothesis testing is planned. Descriptive statistics will summarize baseline demographics, safety endpoints, and other categorical data for all enrolled subjects. For efficacy endpoints, paired t-tests will be used to compare post- vs. pre-procedure HbA1c (%) and other continuous outcomes, and the one-sided 97.5% lower confidence limit of the mean difference will be calculated.

**Interim Analysis**

No interim analysis is planned to stop early for efficacy or futility.

**Subgroup Analysis**

No prespecified subgroup analyses are planned due to the small sample size.

# 7. Monitoring Plan

The monitoring plan includes:

- Pre-study monitoring: investigational product, study documents, study personnel, and training.
- On-study monitoring: routine visits, submissions to the ethics committee during the trial, and AE monitoring.
- End-of-study (or early termination) monitoring: retrieval/destruction of investigational products, EDC/eCRF reconciliation and data queries, verification of document completeness, ethics notifications, site close-out, and clinical study report.

Monitors will conduct periodic on-site reviews to ensure full compliance with the approved protocol/amendments and will review source documents to verify eCRF/EDC entries.

The investigator/institution shall ensure that Shanghai Brattea Medical Technology Co., Ltd., its designees, and relevant regulatory authorities have direct access to source documents (electronic or paper). If original medical records from non-study institutions/providers are not accessible, certified copies of source documents must be provided for review.

# 8. Data Management

Data management will be performed by a CRO and will comply with applicable regulations and the DM department’s SOPs to ensure data are authentic, accurate, complete, and reliable.

## 8.1 Data Entry

Investigators shall collect subject data per protocol and complete the eCRF accurately, timely, completely, and规范ly per the data entry guidelines. The eCRF does not constitute a source document.

## 8.2 Database Setup and Data Verification

An Electronic Data Capture (EDC) system will be used and must comply with FDA 21 CFR Part 11, FDA software validation requirements, and relevant CFDA/NMPA guidance on EDC and clinical data management. eCRFs will be designed by Data Management based on the protocol.

A Data Verification Plan will be prepared according to requirements for completeness, consistency, and accuracy. Logical checks will be programmed/tested and performed via system-automated and manual reviews. Queries generated must be verified and resolved by the investigator or authorized staff.

Queries may also arise during source data review, medical coding, and SAE reconciliation; these processes continue until data cleaning is complete. After cleaning, investigators will electronically sign each eCRF.

The system must maintain an audit trail of any post-save data modifications (who, original value, timestamp, reason). Complete query/audit records shall be retained.

## 8.3 Database Lock

Following the lock procedure, once all pre-lock checks and QC are complete, database lock will be approved in writing; editing privileges and accounts will be revoked, and the Data Manager will lock the database. Any changes after lock must follow formal unlock/re-lock procedures.

After lock, a PDF of each subject’s eCRF containing study data and the audit trail will be generated and archived (e.g., on optical media). All database data and DM documentation will be archived appropriately. As a rule, no changes shall be made to the locked database/files.

### 8.4 Data Processing

After database lock, the statistical team will conduct the statistical analyses.

# 9. Risk–Benefit Analysis

## 9.1 Risks and Adverse Events Related to Endovascular Procedures

Risks are similar to those for patients undergoing comparable vascular interventions outside the study and may include, but are not limited to:

- Allergic reactions (to contrast agents, devices, medications, etc.)
- Access-site complications (bleeding, hematoma, AV fistula, pseudoaneurysm, infection, pain)
- Thrombosis/thrombus formation
- Embolization (air, tissue, thrombus, or material-related)
- Renal impairment or failure
- Pyrexia
- Infection/sepsis
- Vasospasm or occlusion
- Vascular injury (dissection, perforation, rupture, hemorrhage)
- Retroperitoneal hemorrhage
- Vascular complications requiring surgery
- Transient hemodynamic instability (hypotension/hypertensive episodes)
- Arrhythmias
- Cardiopulmonary arrest
- Death

## 9.2 Potential Risks Related to the Investigational Device and EDN

- Potential device/procedure-related risks include:
- Pain
- Celiac/hepatic arterial thrombosis or embolization and resultant end-organ injury
- Celiac/hepatic arterial dissection, perforation, rupture, or bleeding
- Vascular injury or aneurysm formation of the celiac/hepatic arteries
- Vasospasm or acute closure of the celiac/hepatic arteries
- Post-EDN stenosis at ablation sites in the celiac/hepatic arteries
- Hepatic dysfunction
- Gastrointestinal adverse reactions (nausea, vomiting, bloating, diarrhea, etc.)
- Orthostatic hypotension
- Post-procedure hypoglycemia
- Skin burns
- Other unforeseeable risks may also exist.

